## Abstract

**Introduction:**

Coronary artery disease (CAD) and peripheral artery disease (PAD) increase the risks of cardiovascular events and death. Digital health technologies are rapidly expanding to improve healthcare quality and access. The Care4Today Connect (C4T CAD‐PAD) mobile application is designed to help patients with CAD and/or PAD improve medication adherence, learn about their disease, make lifestyle modifications, and enhance healthcare provider (HCP) connection via an HCP‐facing portal.

**Hypothesis & Methods:**

The prospective, single‐arm, multicenter, noninterventional iPACE‐CVD (innovative Patient compAnion impaCting health outcomEs: a CardioVascular Digital health program) study (ClinicalTrials.gov identifier: NCT06052319) is evaluating engagement and usefulness of the application for patients with CAD and/or PAD in clinical settings. Application access is provided with a code from patients' HCPs. Key features include medication and health experience tracking. The application is available in English and Spanish and for iOS and Android devices. Engagement is defined as the proportion of patients who use the application for ≥ 10 weeks during the 3‐month study period. Application use is defined as the number of patients using ≥ 1 application feature(s) each week. Usefulness is determined by the percentage of engaged patients who complete the My Feedback Matters survey with a satisfaction response score of > 2 (on a 5‐point scale, where 1 = *strongly disagree* and 5 = *strongly agree*) for at least three of the six questions.

**Results:**

A total of 271 participants were enrolled between November 29, 2023, and May 15, 2024. The study concluded on August 15, 2024.

**Conclusion:**

This study will help enhance the application for subsequent studies. **Trial Registration:** NCT06052319

AbbreviationsAppapplicationC4TCare4TodayCADcoronary artery diseaseHCPhealthcare providerICFinformed consent formPADperipheral artery disease

## Introduction

1

Coronary artery disease (CAD) and peripheral artery disease (PAD) share risk factors, including lifestyle behaviors (smoking, physical activity, diet, and weight) and health factors (cholesterol levels and blood pressure) [1, 2]. Up to 42% of patients with CAD also have PAD, and the presence of both CAD and PAD further increases the risk of major adverse cardiac events and lower extremity revascularization [3, 4]. Treatment goals for CAD and PAD are aimed at reducing symptoms and preventing future cardiovascular events [5, 6]. Cardiovascular disease burden is even greater in some racial and ethnic minority groups that have not only a higher disease prevalence but also more severe disease and increased risk of adverse events [2, 7, 8, 9, 10, 11, 12]. Addressing cardiovascular risks and disparities among racial and ethnic groups remains an unmet need [13, 14].

Digital health technologies may empower patients to become active participants in their own care through programs that are designed to improve the quality, access, and efficacy of healthcare information [15, 16]. However, there is limited information on digital technologies for cardiovascular disease, particularly for patients with CAD and PAD [17, 18]. To this extent, the Care4Today Connect CAD‐PAD (C4T CAD‐PAD) platform features a patient‐facing digital smartphone application that is designed to help patients with the following: (1) improve medication adherence; (2) acquire knowledge about their disease; (3) embark on lifestyle modifications; (4) track their health; and (5) increase their connection to their healthcare providers (HCPs). The solution allows for the flow of patient‐reported information to their healthcare team via an HCP‐facing portal. Given that this is the first of its kind, there is no information on the usefulness and performance of this type of application regarding patient engagement and satisfaction or the impact of the application on outcomes and quality of life.

The iPACE‐CVD (innovative Patient compAnion impaCting health outcomEs: a CardioVascular Digital health program) study (ClinicalTrials.gov identifier, NCT06052319) will assess engagement and usefulness of the C4T CAD‐PAD smartphone application in patients with CAD and/or PAD.

## Materials and Methods

2

### Study Design and Digital Health Application

2.1

This is a prospective, single‐arm, multicenter (six sites), noninterventional study to assess the C4T CAD‐PAD smartphone application in clinical practice (Figure 1). The study will enroll approximately 150 patients with CAD, 100 with PAD, and 50 with CAD and PAD (polyvascular) based on their most recent diagnoses. Patients will choose to use the C4T CAD‐PAD application over a 3‐month period. All patients must sign an informed consent form (ICF) allowing data reporting and collection in accordance with local requirements and/or the study protocol. The ICF will be completed in the physician's office or remotely (via phone and online portal) and informs patients that no medical care will be provided by the application and that they should consult with their physician for medical advice. The study will be completed virtually, and there is no requirement for the patients to visit a study site. During the virtual onboarding process, patients will be asked to agree to the application's terms of use, privacy policy, and the statement of health information disclosure.

**Figure 1 clc70039-fig-0001:**

Study design of the C4T CAD‐PAD optimization study. App, application; C4T, Care4Today; CAD, coronary artery disease; PAD, peripheral artery disease.

Patients will join the study on their smartphone by using an access code provided by the study site. This code places patients into the C4T CAD‐PAD care module, which is further customized by disease (CAD, PAD, or both), where patients can set a health goal. The site code uniquely connects the patient to their study site via the HCP care portal. Educational articles available to patients will vary based on their designated content module (CAD, PAD, or both). All patients in the study will accumulate and receive points as reimbursement for their time completing study tasks while on the study, the balance of which they will be able to view in the app. The number of points earned by patients throughout the 3‐month engagement period will vary based on their level of involvement in completing applicable engagement activities whether assigned to them or self‐selected by the patient. The points earned during the study will be redeemable at the end of the study.

Patients will use the C4T CAD‐PAD application on a daily or as‐needed basis during the study period to record information on medications, healthcare appointments, health metrics, and lifestyle behaviors as shown in Table 1. The digital health application includes trackers and easy‐to‐follow trend reports for medication adherence, healthcare appointment attendance, and health and lifestyle behaviors (Figure 2).

**Table 1 clc70039-tbl-0001:** Information collected in the C4T CAD‐PAD digital health application used to measure engagement and usefulness.

Information category	Recorded measures
Medication adherence tracker	Medication reminders Missed medications Medication refills
Appointment tracker	Healthcare appointment attendance
Health metrics	Blood pressure Heart rate Blood sugar Hemoglobin A1c Lipid levels
Lifestyle behaviors	Daily routine/function Energy level Smoking (cigarette use tracker) Activity level Sleep Mood Meal rater Leg cramp/discomfort^a^ Encouragement Exercise Daily check‐in Step count Weight Water intake Sodium intake Pain level Nausea

Abbreviations: C4T, Care4Today; CAD, coronary artery disease; PAD, peripheral artery disease.

^a^
The leg cramp/discomfort measure is not limited to patients with PAD and can be recorded by all patients in the study as CAD and PAD often occur together.

**Figure 2 clc70039-fig-0002:**
[figure not shown]
C4T CAD‐PAD screen captures of (A) medication and appointment reminders, (B) health and lifestyle behavior trackers, and (C) easy‐to‐follow trend reports. C4T, Care4Today; CAD, coronary artery disease; PAD, peripheral artery disease.

The C4T CAD‐PAD application includes both scheduled and daily application‐based notification reminders. It is available for both iPhone (iOS) and Android smartphones and in English and Spanish languages. On or after Day 75, patients will be asked to complete a survey to assess overall satisfaction with the application features and educational content. The overall duration of the study for an individual patient is expected to be approximately 3 months.

### Patient Eligibility

2.2

Participating sites will be encouraged to identify eligible patients with CAD and/or PAD based on the inclusion and exclusion criteria listed in Table 2. Male or female patients who are 40−90 years of age (inclusive), have a diagnosis of CAD and/or PAD, and are receiving therapy or about to initiate therapy are eligible. They must own a smartphone, either an iPhone (iPhone 6S or newer; iPhone SE [any generation]) or Android (Android 23, released 2015 or later) and have an active email account. They must sign a participation agreement/ICF allowing data collection in accordance with local requirements and be willing to download and use the C4T CAD‐PAD application. Patients with any cardiovascular or noncardiovascular condition with a poor prognosis, as assessed by the investigator, are not eligible to participate in the study.

**Table 2 clc70039-tbl-0002:** Inclusion and exclusion criteria for participants in the study.

Inclusion criteria	Exclusion criteria
Male or female aged 40−90 years, inclusive Must have a diagnosis of CAD and/or PAD and are on therapy or about to initiate therapy Own a smartphone: ○ iPhone 6s or newer ○ iPhone SE (any generation) ○ Android 23, released in 2015 or later Have an active email account Must sign a participation agreement/ICF allowing data collection in accordance with local requirements Willing to download and use the C4T CAD‐PAD application	Any cardiovascular conditions (e.g., recent stroke, high bleeding risk, and severe heart failure) or noncardiovascular condition deemed as poor prognosis by the investigator and which may prevent a patient from completing the study Unable to read/write English or Spanish Visual/hearing impairment or mental disability that would preclude independent application use Patients currently using the C4T Connect application before signing the ICF

Abbreviations: C4T, Care4Today; CAD, coronary artery disease; ICF, informed consent form; PAD, peripheral artery disease.

### Outcomes

2.3

The primary objectives of this study are: (1) to assess the C4T CAD‐PAD application patient engagement and (2) to understand the usefulness of the C4T CAD‐PAD application to the patients. Patient engagement will be assessed as the proportion of participating patients who use the application for ≥ 10 weeks (~80% of the time) during the 3‐month study period. Weekly application use is defined as the number of patients using ≥ 1 feature of the application once a week. A distribution of participants using more than 1 feature of the application at least once a week will be presented and explored against the current definition of weekly application use. Usefulness will be determined by the percentage of engaged patients who complete the end‐of‐study survey with a satisfaction response score of > 2 (on a 5‐point scale, defined as: 1 = *strongly disagree*, 2 = *disagree*, 3 = *neutral*, 4 = *agree*, and 5 = *strongly agree*) for at least three of the six questions.

Data will be collected directly from the application for all patients by the application developer (Johnson & Johnson Services Inc.). Source data from the application will be made available to the participating clinical sites via the provider portal. All personal information will be deidentified/anonymized before upload to a secure portal for study analysis. The key parameters will include medication adherence, health metrics, and lifestyle behaviors (Table 1). No safety data are collected by study design and, therefore, no safety data analysis will be performed. However, during the study, if a site becomes aware of any incidental safety data involving a Janssen medicinal product, the data will be collected and spontaneously reported.

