### Statistical Methods

2.4

The objective of this study is to explore the engagement and usefulness of the C4T CAD‐PAD digital health application among patients with CAD and/or PAD. In line with pilot investigations, no formal hypothesis has been specified and no formal sample size calculation was conducted [19, 20]. Enrollment of approximately 150 patients with CAD, 100 with PAD, and 50 with both CAD and PAD (polyvascular) is planned to sample a substantial number of representative patients from the broad spectrum of the CAD and/or PAD population and is considered reasonable to meet the exploratory objectives. Because many patients with PAD also have CAD, the PAD and polyvascular groups may be analyzed together in the event that there are challenges in enrolling sufficient numbers of patients with PAD alone.

Analyses of application data will include all patients enrolled in the study and given access to the digital health application. The observation period for data analysis will be from the time of enrollment into the study until the end of the study (3 months or early withdrawal). The main analysis will be using data from all patients obtained through the full observation period of 3 months. Qualitative variables will be summarized by their frequency distributions (counts and percentages) and quantitative variables by their means and standard deviations. Continuous nonnormally distributed variables will be summarized by medians and interquartile ranges and tested for any significant nonnormality using the Kolmogorov−Smirnov test. Where appropriate, such nonnormal data will also be considered for transformation (e.g., logarithmic) before the analysis. The overall percentage of application users in the study by disease diagnosis type will be provided. Point estimates will be provided, as necessary, along with their 95% confidence intervals.

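### The usefulness endpoint passes patients who are neutral or better on half the survey items, so it counts patients who agree with nothing as finding the app useful

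*Protocol article*

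**What the plan says.** Section 2.3 (Outcomes) of the protocol article names as its second primary objective "to understand the usefulness of the C4T CAD‐PAD application to the patients". It defines the measure in one sentence: "Usefulness will be determined by the percentage of engaged patients who complete the" end-of-study survey "with a satisfaction response score of > 2" on the five-point scale, "for at least three of the six questions". The upper part of the scale is given there as "3 = *neutral*, 4 = *agree*, and 5 = *strongly agree". An item therefore passes at 3, 4 or 5, and three passing items are enough.

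The abstract (Hypothesis & Methods) repeats the rule with the same cut-off and item count: "Usefulness is determined by the percentage of engaged patients who complete the My Feedback Matters survey with a satisfaction response score of" more than 2. Neither place gives a reason for the cut-off. Section 2.3 plans to look at an alternative to the definition of weekly use, but names no alternative threshold for usefulness.

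Section 2.4 (Statistical Methods) calls the study exploratory and says that "no formal hypothesis has been specified and no formal sample size calculation was conducted".

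**The concern.** A neutral answer is neither agreement nor satisfaction, yet the rule treats it as a satisfied item. Because half the items suffice, the remaining three can be strongly negative without changing the patient's classification. The percentage is named usefulness but describes absence of a negative answer on at least half the questions.

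In a descriptive study the reported percentage is itself the result. Sections 4 (Discussion) and 5 (Conclusions) look to this study for information on usefulness, and the Discussion says it should help improve the application before a later study of clinical outcomes. A headline figure that merges indifference with approval would serve that purpose poorly and could be read as endorsement.

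**Working it through.** The article gives no expected usefulness rate, so there is no figure to reproduce. The check has two parts.

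**1. What the rule admits (no response distribution needed).** The inputs, all from section 2.3, are six items scored 1 to 5, an item passing at 3 or more, and a patient passing with at least three passing items.

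- Neutral on all six items: passes.
- Neutral on three and strongly disagree on three: mean (3×3 + 3×1)/6 = 2.0, which is the score for disagree. Passes.
- All possible response patterns: 5^6 = 15,625.
- Passing patterns (three passing scores and two failing scores per item): C(6,3)·3³·2³ + C(6,4)·3⁴·2² + C(6,5)·3⁵·2 + 3⁶ = 4,320 + 4,860 + 2,916 + 729 = 12,825.
- Passing patterns with no 4 or 5 anywhere: 20·8 + 15·4 + 6·2 + 1 = 233.
- Passing patterns with a mean below 3, by enumeration: 4,152, or 4,152/12,825 = 32.4%.

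These are counts of patterns, not forecasts of patients.

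**2. How far the percentage could move (assumed distributions).** With p the chance that one item passes and items independent, P(pass) = P(X ≥ 3) for X ~ Binomial(6, p) = 1 − [(1−p)⁶ + 6p(1−p)⁵ + 15p²(1−p)⁴].

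- p = 0.8: 1 − (0.000064 + 0.001536 + 0.01536) = 0.983
- p = 0.6: 1 − (0.004096 + 0.036864 + 0.13824) = 0.821
- p = 0.4: 1 − (0.046656 + 0.186624 + 0.31104) = 0.456
- p = 0.3: 1 − (0.117649 + 0.302526 + 0.324135) = 0.256

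Both columns below require three of six items.

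| Assumed answers per item | Stated rule (> 2) | 4 or 5 |
|---|---|---|
| 20% negative, 20% neutral, 60% agree | p = 0.8: 98% | p = 0.6: 82% |
| Uniform over 1 to 5 | p = 0.6: 82% | p = 0.4: 46% |
| 20/20/30/20/10% over 1 to 5 (mean 2.8) | p = 0.6: 82% | p = 0.3: 26% |
| 50% negative, 50% neutral, none agree | p = 0.5: 66% | p = 0: 0% |

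Rows two and three give the same 82% under the stated rule although agreement falls from 40% to 30% of answers. The rule does not register a move between neutral and agree.

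**Correlation.** Six items answered by one person about one app are unlikely to be independent. In a latent-normal model with equal inter-item correlation 0.5, the uniform case becomes 69% v 44% and the 20/20/30/20/10 case about 69% v 31%. In the latter the gap falls from about 57 points to 38, but it does not close.

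**The case against.** **The study is exploratory.** There is no hypothesis, and the article states no success threshold or go/no-go rule for usefulness. Section 4.1 (Study Limitations) says that only descriptive information will be provided. This stands: no test or error rate is affected, which limits the consequence. It does not make the label accurate.

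**The rule is stated openly.** A careful reader can see that neutral passes. That is true of this article, but a later report may carry only the percentage and its name.

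**The unfavourable distributions are hypothetical.** The measure concerns engaged patients, who used the app for at least 10 weeks, so favourable answers are plausible, and the 98% v 82% case may be nearer to what is seen. This stands, and the size must be given as a range.

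**Item tables may already be planned.** Section 2.4 promises counts and percentages for qualitative variables and 95% confidence intervals as necessary. Item-level tables fit under that and cannot be called absent. They would not change what is headlined as usefulness.

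**Changing the rule now would be post hoc.** Section 3 (Results) gives August 15, 2024 as study completion. This stands, and it rules out replacing the prespecified definition.

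A reader might also infer that a high percentage is all but certain whatever patients think. The article does not support that. If only 20% of answers exceed 2, the stated rule gives about 10%; at 30% it gives 26%. The percentage does move with opinion, and the item responses remain available to guide changes to the app.

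**Conclusion.** The point holds as a matter of construct and labelling, and should be fixed. It is certain from the definition that patients expressing no agreement can be counted as finding the app useful. The only premise is that items are worded so that agreement is favourable. The item texts are not shown, but the article's description of the response as a satisfaction score supports this.

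The size of the inflation is not known. In the cases with some agreement and independent items, the stated rule exceeds the 4-or-5 rule by about 16 points (favourable answers) to 57 points (20/20/30/20/10). The assumed distributions are illustrations, not estimates for this population.

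**What to change.** - Keep and report the prespecified result, labelled as neutral or better on at least three of six items, and not as usefulness or satisfaction.
- Report beside it, with a 95% confidence interval, the percentage scoring 4 or 5 on at least three of six items. Base any statement that patients found the app useful on that figure. If it was added after data were seen, mark it as post hoc.
- Show the response distribution for each of the six items.

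No new data are needed. The cost is a change of label, one extra table and a lower headline percentage.

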### Statistical Methods

2.4

The objective of this study is to explore the engagement and usefulness of the C4T CAD‐PAD digital health application among patients with CAD and/or PAD. In line with pilot investigations, no formal hypothesis has been specified and no formal sample size calculation was conducted [19, 20]. Enrollment of approximately 150 patients with CAD, 100 with PAD, and 50 with both CAD and PAD (polyvascular) is planned to sample a substantial number of representative patients from the broad spectrum of the CAD and/or PAD population and is considered reasonable to meet the exploratory objectives. Because many patients with PAD also have CAD, the PAD and polyvascular groups may be analyzed together in the event that there are challenges in enrolling sufficient numbers of patients with PAD alone.

Analyses of application data will include all patients enrolled in the study and given access to the digital health application. The observation period for data analysis will be from the time of enrollment into the study until the end of the study (3 months or early withdrawal). The main analysis will be using data from all patients obtained through the full observation period of 3 months. Qualitative variables will be summarized by their frequency distributions (counts and percentages) and quantitative variables by their means and standard deviations. Continuous nonnormally distributed variables will be summarized by medians and interquartile ranges and tested for any significant nonnormality using the Kolmogorov−Smirnov test. Where appropriate, such nonnormal data will also be considered for transformation (e.g., logarithmic) before the analysis. The overall percentage of application users in the study by disease diagnosis type will be provided. Point estimates will be provided, as necessary, along with their 95% confidence intervals.

### Study Organization

2.5

This study is sponsored by Janssen Scientific Affairs, LLC. An independent steering committee composed of members including sponsor representatives, experts in the management of CAD‐PAD patients, experts in digital health technology, and advocacy representatives provided oversight.

## Results

3

Patients were enrolled from November 29, 2023, to May 15, 2024. A total of 271 patients were enrolled. Of these, 59% were male, 40% were female, and 1% preferred not to disclose their sex. The study was completed on August 15, 2024.

